### 7.1.6 Safety Parameters

Clinical findings, physical examination findings, laboratory examination findings

**7.2 SCHEDULE OF TIME AND EVENTS**

Each laboratory test and clinical observation will be performed according to the study schedule in Table 2

Table 2 Study schedule

|  | Day-7 | Phase I | | >4  weeks | Phase II | | >4  weeks | Phase III | |
| --- | --- | --- | --- | --- | --- | --- | --- | --- | --- |
| 1-Day-1 | 1-Day0~1-Day+2 | Washout Period | 2-Day-1 | 2-Day0 ~  2-Day+2 | Washout Period | 3-Day-1 | 3-Day0~  3-Day+2 |
| Screening | Pre-dose | Dosing and  blood sampling  (until 48 h) | Pre-dose | Dosing and blood sampling (until 48 h) | Pre-dose | Dosing and blood sampling  (until 48 h) |
| Informed consent | 〇 |  |  |  |  |  |  |
| Enrollment |  | 〇 |  |  |  |  |  |
| Allocation |  | 〇 |  |  |  |  |  |
| Demographics | 〇 |  |  |  |  |  |  |
| Height, weight, BMI | 〇 |  |  |  |  |  |  |
| Blood pressure, pulse, body temperature | 〇 | 〇 | 〇 | 〇 | 〇 | 〇 | 〇 |
| Clinical examination | 〇 | 〇 | 〇 | 〇 | 〇 | 〇 | 〇 |
| Urine pregnancy test | 〇 |  |  | 〇 |  | 〇 |  |
| Lab tests | 〇 | 〇 | 〇 | 〇 | 〇 | 〇 | 〇 |
| TJ-43 administration  Group A  Group B  Group C |  |  | 〇  7.5 g  2.5 g  5 g |  | 〇  2.5 g  5 g  7.5 g |  | 〇  5 g  7.5 g  2.5 g |
| Pharmacokinetics |  |  | 〇 |  | 〇 |  | 〇 |
| Safety  assessment |  |  |  |  |  |  |  |  |  |

Each laboratory test and clinical observation will be performed according to the study schedule in Table 3 (sample time schedule is shown).

Table 3 Study Schedule 2 (each phase)Note1

|  | Day  -7 | Day  -1 | Day 0 | | | | | | | | | | | | Day  +1 | Day  +2 |
| --- | --- | --- | --- | --- | --- | --- | --- | --- | --- | --- | --- | --- | --- | --- | --- | --- |
| Screening | Pre-dosing | Immediately before dosing | 0  h | 15  min | 30  min | 1  h | 2  h | 3  h | 4  h | 6  h | 8  h | 10  h | 12  h | 24  h | 48  h |
| 7:  30 | 8:  00 | 8:  15 | 8:  30 | 9:  00 | 10:00 | 11:00 | 12:00 | 14:00 | 16:00 | 18:00 | 20:00 | 8:  00 | 8:  00 |
| Informed consent | ○ |  |  |  |  |  |  |  |  |  |  |  |  |  |  |  |
| Subject roster |  | ○ |  |  |  |  |  |  |  |  |  |  |  |  |  |  |
| Allocation |  | ○ |  |  |  |  |  |  |  |  |  |  |  |  |  |  |
| Demographics | ○ |  |  |  |  |  |  |  |  |  |  |  |  |  |  |  |
| Height, weight,  BMI | ○ |  |  |  |  |  |  |  |  |  |  |  |  |  |  |  |
| Blood pressure, pulse,  body temperature | ○ | ○ |  |  |  |  |  |  |  |  |  |  |  |  |  | ○ |
| Clinical examination | ○ | ○ |  |  |  |  |  |  |  |  |  |  |  |  |  | ○ |
| Urine pregnancy testNote2 | ○ | |  |  |  |  |  |  |  |  |  |  |  |  |  |  |
| Lab testsNote3  sample volume | ○  8 mL | ○  8 mL |  |  |  |  |  |  |  |  |  |  |  |  |  | ○  8 mL |
| TJ-43 dosing |  |  |  | ○ |  |  |  |  |  |  |  |  |  |  |  |  |
| MealNote4 |  | ○ |  |  |  |  |  |  |  | ○ |  |  | ○ |  | ○ | ○ |
| PKNote3  sample volume |  |  | ○  12 mL |  | ○  12 mL | ○  12 mL | ○  12 mL | ○  12 mL | ○  12 mL | ○  12 mL | ○  12 mL | ○  12 mL | ○  12 mL | ○  12 mL | ○  12 mL | ○  12 mL |
| Safety assessment |  |  |  |  |  |  |  |  |  |  |  |  |  |  |  |  |

Note 1: The schedule is for phase I. Screening tests conducted 7 days prior to administration of TJ-43 will not be performed in phases II and III, whereas pre-dose tests conducted 1 day prior to administration and other tests scheduled thereafter will be performed.

Note 2: This will be conducted in females only. It will be performed at the time of screening in phase I. It will be conducted 1 day prior to administration of J-43 in phases II and III.

Note 3: The total blood drawn will be 524 mL {screening: 8 mL × 1, 172 mL for each of the 3 phases [(8 mL × 2 for laboratory tests, 12 mL × 13 for pharmacokinetic) × 3]}. In addition, general urinalysis (urine sugar) will be performed at the time of screening only.

Note 4: Foods and drinks (including spices) (see attached reference) containing caffeine, alcohol, citrus fruits (grapefruit, orange, tangerine, etc.), vitamin P, ginseng, ginger, kanzo (listed on a food label), and garlic are prohibited from 3 days prior to study drug administration until completion of each treatment phase of the study. Supplements containing constituents of rikkunshito (Atractylodes Lancea Rhizome, Ginseng, Pinellia Tuber, Poria Sclerotium, Jujube, Citrus Unshiu Peel, Glycyrrhiza, and Ginger), Processed Ginger, and vitamin P are also prohibited. However foods and drinks that do not contain the above (see attached references) may be consumed at any time. Subjects must have fasted from 20:00 on the eve of study drug administration to 4 h post-dose.

**8. CRITERIA FOR EVALUATION AND ANALYSIS**

**8.1 TARGET POPULATION**

**8.1.1 Target Population for Pharmacokinetic Analysis**

Registered subjects who satisfy the inclusion criteria and do not meet the exclusion criteria as well as those who have completed sampling for pharmacokinetic analysis after administration of the study drug

**8.1.2 Target Population for Safety Analysis**

Subjects who have taken the study drug

**8.2 ENDPOINTS**

**8.2.1 Pharmacokinetics**

Pharmacokinetics will be evaluated using the collected blood samples by measuring plasma concentration of 8 constituents (atractylodin, pachymic acid, heptamethoxyflavone, liquiritigenin, isoliquiritigenin, nobiletin, naringenin, and glycyrrhetinic acid) and calculating pharmacokinetic parameters such as maximum drug concentration in plasma (*C*max), maximum drug concentration time in plasma (*t*max), and area under the blood concentration–time curve (AUC) from plasma concentration of the 8 constituents for which validated analytical methods have been established.

The detailed method of plasma concentration analysis of the 8 constituents will be written in the study plan, which will be prepared separately. Shin Nippon Biomedical Laboratories and Mitsubishi Medical Medience will perform the analyses; however, additional analyses, including preliminary metabolite screening, will be conducted as required.

The details of pharmacokinetic analyses will be documented in the pharmacokinetic analysis plan, which will be prepared separately. Tsumura Laboratories will perform pharmacokinetic analysis by following this document. Data from blood collected outside the sampling windows will be handled as described in the pharmacokinetic analysis plan.

Various pharmacokinetic data, including plasma concentration measurements, may be used for separate analysis at a later time.

The concentration of the 8 constituents in TJ-43 drug lots used for pharmacokinetic analysis will be obtained when plasma concentration analysis of the TJ-43 lot is performed by Sumika Chemical Analysis Service, LTD.

**8.2.2 Safety Assessment**

Safety will be comprehensively evaluated from the overall assessment of clinical findings, physical examination, and laboratory tests performed prior to and during the study. The results of these tests performed before administration of the study drug will become the baseline values and changes observed after dosing will be compared with these baseline values.

[Abnormal changes]

-The principal investigator will compare the values obtained before dosing with those obtained after dosing; if the change between the two values is more than 20%, it will be considered as an abnormal change.

-Abnormal changes will be handled as AEs and recorded in the AE list.

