**7.1.4 Tests at the End of the Study**

At the end of each treatment phase, the principal investigator/subinvestigator will perform the following clinical observations and laboratory tests.

Clinical findings: subjective symptoms, objective findings, edema

Physical examination: body temperature (axillary), blood pressure (seated), pulse (seated)

Laboratory tests: 1) Hematology

erythrocytes, leukocytes, platelets, hemoglobin, hematocrit

2) Blood chemistry

total protein, BUN, creatinine, uric acid, AST, ALT, T-Bil, ALP, γ-GTP, Alb, PT, TC, CRP, K

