**9 ADVERSE EVENTS**

**9.1 DEFINITION**

**9.1.1 Adverse Events**

An AE is any unfavorable or unintended medical sign (including abnormal laboratory values), symptom, or disease in a subject following exposure to the study drug, regardless of a causal relationship with the study drug. A condition that develops during the study is also included.

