**9.2 MONITORING ADVERSE EVENTS**

Any AE must be investigated through inquiry and observation, and if confirmed, the event must be followed and details regarding the following items must be documented in the CRF.

i) type of AE

ii) date of onset

iii) seriousness (1. non-serious, 2. serious)

iv) rationale for seriousness and other medically significant events

v) severity (1. mild, 2. moderate, 3. severe)

vi) treatment (description of intervention if implemented)

vii) outcome [1. recovery (resolution), 2. remission, 3. irresolution (unchanged), 4. complication, 5. unknown]

viii) date of verified outcome

ix) causality (1. definitely related, 2. possibly related, 3. possibly unrelated, 4. not related)

The principal investigator/subinvestigator must document clinically significant, abnormal changes in laboratory test values and their explanations in the CRF.

Causality assessment between the AE and study drug must be documented in the CRF.

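### Section 8.2.2 makes every pre/post change above 20% an automatic AE, so AE and ADR counts would largely reflect normal variation; the rule also does not match 9.1.1 and 9.2

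*Protocol*

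**What the plan says.** Safety is one of the two stated objectives (Protocol 1.2 and 3.1). Section 8.2.2 bases it on the "overall assessment of clinical findings, physical examination, and laboratory tests performed prior to and during the study". It then fixes the comparison: "The results of these tests performed before administration of the study drug will become the baseline values".

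Under the label for abnormal changes, the same section says that "if the change between the two values is more than 20%, it will be considered as an abnormal change", and then: "Abnormal changes will be handled as AEs and recorded in the AE list". It gives no direction, reference range, test-specific limit or clinical filter.

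The tests repeated at the end of each phase (7.1.4) are haematology ("erythrocytes, leukocytes, platelets, hemoglobin, hematocrit"), chemistry ("total protein, BUN, creatinine, uric acid, AST, ALT, T-Bil, ALP, γ-GTP, Alb, PT, TC, CRP, K") and the vital signs.

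Two other sections bear on the same values:

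- 9.1.1: "An AE is any unfavorable or unintended medical sign (including abnormal laboratory values), symptom, or disease". There is no 20% condition.
- 9.2: the investigator "must document clinically significant, abnormal changes in laboratory test values and their explanations in the CRF". Here the criterion is clinical significance.

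**The concern.** A single relative threshold suits few of these tests. A variable analyte such as CRP, bilirubin or ALT can move by a fifth between two draws with no drug effect and stay within normal limits. It can also move in the favourable direction. Section 8.2.2 makes each of these an AE.

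The noise does not stop at the AE list. Under 9.1.3 and 9.1.4, an AE in any of the first three of the four causality classes counts as an ADR. The fourth class needs another plausible explanation, such as concurrent illness or medication, which healthy, unmedicated volunteers will seldom supply. Under 9.2.1, unexpected ADRs are reported to the authorities even when non-serious. All three periods are active doses (5.2, Table 1), so no untreated period shows how many flags arise without drug.

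Only the protocol is at hand. This is a recording rule that the investigator applies during the study, and the protocol already fixes it, so it is not a detail left to an analysis plan.

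**Working it through.** The protocol states no false-flag rate or expected AE count, so there is no figure to reproduce. The check asks how often the rule fires when the drug does nothing.

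**Number of comparisons**

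- Laboratory values per phase end (7.1.4): 5 haematology + 14 chemistry = 19.
- Vital signs (7.1.4): temperature, pulse, systolic and diastolic pressure = 4. Counting the two pressures separately, and including vital signs at all, are assumptions.
- Subject-phases: 21 (4.2) × 3 (5.3.1) = 63.
- Total: 23 × 63 = 1,449. With laboratory values only: 19 × 63 = 1,197.

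**Chance of a flag per comparison**

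Assume two log-normal readings with the same mean and a total within-subject CV of c. The SD of the log ratio is s = √(2·ln(1 + c²)). Then

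P(flag) = Φ(ln 0.8 / s) + 1 − Φ(ln 1.2 / s).

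At c = 10%: s = √(2·ln 1.01) = 0.1411; ln 0.8 / s = −1.582; ln 1.2 / s = 1.292; P = 0.0568 + 0.0981 ≈ 0.155.

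| Assumed CV | s | Fall >20% | Rise >20% | P(flag) | Expected flags per test, 63 phases |
|---|---|---|---|---|---|
| 5% | 0.0707 | 0.0008 | 0.0049 | 0.0057 | 0.4 |
| 10% | 0.1411 | 0.0568 | 0.0981 | 0.155 | 9.8 |
| 20% | 0.2801 | 0.2128 | 0.2575 | 0.470 | 29.6 |
| 40% | 0.5448 | 0.3411 | 0.3689 | 0.710 | 44.7 |

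At 7% the chance is 4.5%, so it passes 5% once the CV exceeds about 7%.

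**Whole study, 23 values**

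- All CVs 5%: 23 × 0.0057 × 63 ≈ 8 spurious AEs.
- Lower mix (8 values at 3%, 9 at 7%, 4 at 10%, 2 at 20%): (0.000 + 0.401 + 0.620 + 0.941) × 63 = 1.962 × 63 ≈ 124.
- Middle mix (8 at 4%, 7 at 10%, 5 at 15%, 3 at 30%): (0.005 + 1.085 + 1.694 + 1.877) × 63 = 4.661 × 63 ≈ 294.

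If the values are also taken as independent, about 33% of subjects have at least one spurious AE in the first case, and nearly all do in the two mixes.

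**Tightly regulated values** (baselines assumed)

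- Temperature 36.5 °C: a flag needs more than 36.5 × 1.2 = 43.8 °C or less than 36.5 × 0.8 = 29.2 °C. If the rule covers temperature, it carries no information there.
- Potassium 4.0: a flag needs less than 3.2 or more than 4.8. A fall from 4.2 to 3.4 (3.4 / 4.2 = 0.81, or −19%) is not flagged. The rule is coarse for potassium but can fire.

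**The three criteria side by side**

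Section 8.2.2 uses the size of the change, 9.1.1 an unfavourable or unintended sign, and 9.2 clinical significance. No sentence ranks them.

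**The case against.** A reader might infer that the safety result will be wrong in both directions, because the rule cannot see a potassium fall or a fever. The protocol does not support that. Section 8.2.2 says a change above 20% is abnormal; it does not say a smaller one is normal. Section 9.1.1 makes abnormal laboratory values AEs with no 20% condition, and 9.2 separately requires clinically significant laboratory changes to be documented. Under-counting arises only if a site treats 8.2.2 as the sole criterion. The pseudoaldosteronism named in the Background is tied there to long-term use of large amounts of Glycyrrhiza, whereas this study gives three single doses more than four weeks apart.

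A reader might also infer that noise could end the study. Section 10.7.2 limits that criterion to frequent AEs that undermine continuation, and the sponsor consults the principal investigator. Likewise, an AE becomes an ADR only after case-by-case assessment, and a not-related class exists.

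Other points on that side also stand. Sections 9.2 and 13.1 use the term abnormal changes for laboratory values, so the rule may not extend to vital signs. The definition in 9.1.1 covers unintended as well as unfavourable signs, and 9.2 does not say that only clinically significant changes are AEs, so the three texts are unharmonised rather than flatly opposed. No hypothesis test or sample size rests on AE counts, the pharmacokinetic results are untouched, and the measured values stay available for re-evaluation.

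None of this removes the over-counting. A site that follows 8.2.2 as written must list every change above 20%, and dropping vital signs leaves 1,197 comparisons.

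**Conclusion.** The concern holds for over-counting and for the lack of a governing criterion. Followed as written, 8.2.2 turns ordinary and even favourable variation into AEs, and AE and ADR counts would largely reflect that variation for any test whose within-subject CV is above about 7%. The size is a range: about 8 spurious AEs if every CV is 5%, and about 120 to 290 under the two mixes. It rests on assumed CVs, log-normal readings, no drug effect, and 23 values in 21 subjects over 3 phases. Only the uniformly low-CV case makes the problem small.

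The threshold is uninformative for body temperature, if it applies there, and coarse for potassium. That is a secondary weakness, because 9.1.1 and 9.2 still allow smaller abnormal changes to be recorded.

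**What to change.** Reconcile 8.2.2, 9.1.1 and 9.2 as follows:

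- Delete from 8.2.2 the sentence that turns abnormal changes into AEs automatically.
- Keep the 20% change as a descriptive flag that prompts investigator review, and list it separately from AEs.
- Let AE status for laboratory values and vital signs follow 9.1.1: unfavourable or unintended, including values abnormal against the institution's reference range.
- Document clinical significance as 9.2 requires, but do not make it a further condition for being an AE. That would be narrower than 9.1.1 and would drop out-of-range values judged not significant.
- State whether the flag covers vital signs.

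The cost is protocol wording and a matching CRF instruction. No new data or visits are needed. The downside is more reliance on reference ranges and investigator judgement.

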**8.2.3 Fixation of the Analysis Set**

The sponsor will fix the target population for pharmacokinetic-related analysis and safety-related analysis according to Tsumura-GCP/SOP/11.

**8.3 STATISTICAL ANALYSIS PLAN**

Methods for identifying and classifying the endpoints for analysis, as well as the timeframe and methods for conducting analyses, should follow the “Statistical Analysis Plan (Appendix 2).” Furthermore, statistical analysis will be performed when the guideline for statistical analysis is prepared. Pharmacokinetics will be analyzed according to the Pharmacokinetic Analysis Plan, which will be prepared separately from the “Statistical Analysis Plan (Appendix 2).”

**9 ADVERSE EVENTS**

**9.1 DEFINITION**

**9.1.1 Adverse Events**

An AE is any unfavorable or unintended medical sign (including abnormal laboratory values), symptom, or disease in a subject following exposure to the study drug, regardless of a causal relationship with the study drug. A condition that develops during the study is also included.

**9.1.2 Serious Adverse Event**

A serious adverse event (SAE) is defined as an AE that results in any of the following outcomes:

(1) Death

(2) A life-threatening condition

(3) Hospitalization or prolongation of existing hospitalization

(4) Persistent or significant disability/incapacity

(5) A congenital anomaly or birth defect

(6) Another medically significant event

**9.1.3 Adverse Drug Reaction**

An ADR is defined as an AE for which a causal relationship with the study drug cannot be ruled out (refer to sections 1)–3) of 9.1.4 Causality Assessment).

**9.1.4 Causality Assessment**

The following criteria will be used to characterize causality into 4 classes:

[Causality Classification]

1) Definitely Related

There is evidence to suggest a plausible temporal relationship (including follow-up after termination of treatment) between the study drug and AE. Sufficient evidence to support this relationship is also found.

2) Possibly Related

There is evidence to suggest a reasonable temporal relationship (including follow-up after termination of treatment) between the study drug and AE. The AE is unlikely to be attributed to factors other than the study drug.

3) Possibly Unrelated

There is evidence to suggest a reasonable temporal relationship (including follow-up after termination of treatment) between the study drug and AE. However, factors such as underlying disease, concurrent illness, and concurrent medication/intervention may also be implicated.

4) Not Related

A temporal relationship between the study drug and AE is improbable because other factors such as underlying disease, concurrent illness, and concurrent medication/intervention provide plausible explanations; thus, there is enough evidence to exclude the involvement of the study drug.

**9.1.5 Severity of Adverse Events**

1) Mild:

The event is generally temporary; it does not impair the person’s ability to conduct normal life functions (i.e., normal activities are possible) and does not require treatment.

2) Moderate

The event interferes with the person’s ability to conduct normal life functions (i.e., normal activities are accompanied by discomfort) and requires treatment.

3) Severe

The event severely impairs the person’s ability to conduct normal life functions (i.e., normal activities are onerous) and requires treatment.

**9.2 MONITORING ADVERSE EVENTS**

Any AE must be investigated through inquiry and observation, and if confirmed, the event must be followed and details regarding the following items must be documented in the CRF.

i) type of AE

ii) date of onset

iii) seriousness (1. non-serious, 2. serious)

iv) rationale for seriousness and other medically significant events

v) severity (1. mild, 2. moderate, 3. severe)

vi) treatment (description of intervention if implemented)

vii) outcome [1. recovery (resolution), 2. remission, 3. irresolution (unchanged), 4. complication, 5. unknown]

viii) date of verified outcome

ix) causality (1. definitely related, 2. possibly related, 3. possibly unrelated, 4. not related)

The principal investigator/subinvestigator must document clinically significant, abnormal changes in laboratory test values and their explanations in the CRF.

Causality assessment between the AE and study drug must be documented in the CRF.

**9.2.1 Handling of Adverse Events**

Regardless of causality, the principal investigator must promptly (within 24 h) report any AE considered to be serious (according to the criteria in section 9.1.2) to the affiliated institution head/institutional review board (IRB) and sponsor in person, by telephone, or by fax, take appropriate actions, and also submit a written “Serious Adverse Event Report Form (Form 3)” within few days of the event. In addition, the principal investigator/subinvestigator must provide additional information to the sponsor, institution head, and IRB upon request.

The institution head must seek IRB’s assessment of the institution’s competence to continue the study and take the necessary steps.

The sponsor must immediately report expected serious ADRs according to the package insert and unexpected serious or non-serious ADRs in suspected subjects to the appropriate regulatory agencies in accordance with Tsumura-GCP/SOP and Tsumura-GPSP/SOP, as well as Article 77, Paragraph 4, Item 2, and Article 253 of the Pharmaceutical Affairs Act.

**9.3 SUBMISSION OF NEW INFORMATION**

Upon receipt of new information regarding product document revisions, safety of the study drug, etc., the sponsor must promptly notify the institution head/IRB and the principal investigator in writing and take the necessary measures.

**9.4 EXPECTED ADVERSE DRUG REACTIONS**

Refer to the product document “Tsumura Rikkunshito Extract Granule (Prescription) Package Insert.”

**10. ETHICAL CONSIDERATIONS**

**10.1 COMPLIANCE WITH ETHICAL PRINCIPLES**

This study will be conducted in accordance with the spirit of the Declaration of Helsinki, the study protocol, the standards specified under the Pharmaceutical Affairs Act Article 80, Paragraph 2, GCP effective as of April 1, 1997 (Ministry of Health and Welfare Ordinance No. 28), and the related ministerial ordinances and notifications.

In addition, the study protocol, etc., will be periodically revised if necessary.

**10.2 INSTITUTIONAL REVIEW BOARD**

Prior to beginning the study, the IRB of the institution will examine the study protocol, CRF format, elements of the written informed consent form, and adequacy of study duration.

